***Method****.* Using a randomized controlled design, 58 women will be randomized to receive either TAICBT treatment or assigned to a 7-10 week WLC. Participants assigned to the WLC will receive a pamphlet that includes information on information on PPD and websites for support services offered in Saskatchewan. The intervention will consist of a seven-module TAICBT program adapted for women afflicted with PPD. Each TAICBT participant will be assigned to a therapist who they can correspond with weekly via email. Potential participants will be screened using the **Edinburgh Postnatal Depression Scale** (EPDS; Cox et al., 1987), modules from the **MINI International Neuropsychiatric Interview** (Sheehan et al., 1998), as well as standard screening questions. If deemed eligible, the following additional outcome measures will be administered: (a)**Depression Anxiety Stress Scale- Short Form** (DASS; Lovibond & Lovibond, 1995) to measure levels of depression, stress, and anxiety; (b)**Parenting Stress Index- Short Form** (PSI-SF; Abidin, 1995) to assess stress in the parent-child system; (c) **World Health Organization Quality of Life – BREF** (WHOQOL-BREF; WHOQOL Group, 1998) to assess quality of life;(d) **Therapist Alliance Questionnaire** (TAQ; Kiropoulos et al., 2008, modified from Luborsky’s 1985 HAQ-II) to determine the degree to which participants perceive the relationship with their therapist as helpful; (e) **Treatment Satisfaction Questionnaire-Modified** (TSQ; Cox et al., 1994) to assess the client’s perceived satisfaction with treatment; and (f) **Credibility/Expectancy Questionnaire**(CEQ; Devilly & Borkovec, 2000) to measure credibility and treatment expectancy of the TAICBT treatment. The TAQ, TSQ, and CEQ will only be completed by those participants receiving TAICBT treatment. All other measures will be completed by both groups of participants at pre-treatment and post-treatment (10 weeks after baseline). Following the 7-10 week wait, participants in the WLC group will be contacted, re-screened, and if still eligible, they will be offered the treatment. At this time, the TAICBT participants will be asked to respond to ten open-ended questions regarding their experiences with the program. To provide a longer-term follow-up of depressive symptoms, TAICBT participants will be contacted by telephone four weeks following treatment completion and administered the EPDS and the depression module of the MINI.

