# Section II: Application Checklist

1. Do you consider that this project involves:

HIGH RISK to subjects

MORE THAN MINIMUM RISK to subjects

MINIMUM RISK to subjects

Researchers are advised that "Risk" is defined broadly to include not only threats to one's physical integrity or health but also temporary as well as permanent psychosocial consequences (e.g., experiencing negative mood for a brief period as a result of research participation, potential for violations of privacy, potential for upsetting a third party because of research participation).

If other than MINIMUM RISK, please explain and submit the full research proposal (e.g., grant application, thesis proposal) or, if a full proposal is not available, contact the REB Chair.

We have classified this research as minimum risk. Clients will either be assigned to a waiting list condition or an intervention condition. In the waiting list condition, clients are free to receive usual care. Furthermore, we will be providing them a pamphlet that has been designed to assist women with PPD with accessing care in Saskatchewan. Clients who are assigned to the intervention condition, will be receiving treatment that has been found to be helpful for clients who have depression, and, therefore the program is anticipated to actually reduce risk. Following the 10-week wait time, participants in the waitlist group will be re-screened, and if they still meet eligibility criteria for the study, they will be offered the opportunity to receive TAICBT treatment.

Clients who receive TAICBT, will be communicating with their therapists over the onlinetherapyuser website. There are multiple safeguards in place to ensure that information is protected and kept securely (see below).

The REB reserves the right to request a copy of the full research proposal for any project that is assessed (by any one of the reviewers of the application) as involving more than minimum risk.

2 What are the sources of funding (if any) for the proposed research?

[name] is funded by the Canadian Institutes of Health Research’s Regional Partnerships Program (CIHR-RPP) and the Saskatchewan Health Research Foundation. Her supervisor [name] and the Online Therapy Unit are funded by the Canadian Institutes of Health Research and the Saskatchewan Health Research Foundation.

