***TAICBT treatment***: Following completion of the baseline measures, the participants in the TAICBT condition will be provided with a login username and password to access Maternal Depression Online, which will be located at the following address: <http://www.onlinetherapyuser.ca>. As part of clinical practice, with client consent, a letter will be sent to the participant’s family physician informing them that their patient is participating in the Maternal Depression Online program (see Appendix N). This is done for two reasons. The first is to verify the client’s identity, and the second reason is to have a contact number in the unlikely case of an emergency. Upon initial login to the website, participants are provided with an information page and consent form (see Appendix G). The participants will then be offered the seven-module online treatment, with each module taking approximately one week to complete. Each module provides education about the disorder and assigns suggested exercises and homework to be completed in consort with an online therapist. The therapist communicates with their client once a week through emails that are contained within the Online Therapy USER website. Upon login for a new module, participants complete a weekly mood monitor (see Appendix O) and provide examples and answers questions from the previous module (see Introduction pages from http://www.onlinetherapyuser.ca/sitemap).

In order to assess change over time, following treatment completion, participants will be emailed the same website link to fluidsurvey.com to complete the post-treatment outcome measures along with measures related to therapeutic alliance (see Appendices H to M). The measures will take approximately 30-45 minutes to complete and will assess change in symptoms over the course of treatment. In addition to the measures, the participants will be asked to respond to a series of follow-up, open-ended questions regarding their experiences with the program (see Appendix P) as well as questions regarding any additional treatment they sought over the 10-week period (see Appendix O).

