***Pamphlet Condition***. In similar fashion to the TAU condition used in Austin and colleagues’ (2008) study, the participants who are randomly assigned to the TAU group will receive an information pamphlet that will be delivered via email (see Appendix Q). The MotherFirst campaign created an information pamphlet that is currently available to Saskatchewan healthcare providers, various support groups, and is displayed in places frequented by new mothers and their families. The chair of MotherFirst has agreed that the MotherFirst information pamphlet can be used for the purpose of the TAU condition. The pamphlet contains information on PPD symptoms and strategies to prevent and/or manage such symptoms. The pamphlet also includes a contact number and a website for postnatal support services offered in Saskatchewan (skmaternalmentalhealth.ca). Participants will be briefed over the telephone with the pamphlet information and informed of the postnatal support contacts should they choose to receive treatment. Seven to ten weeks following baseline measures, the participants will be emailed the same website link to fluidsurvey.com to complete the post-treatment outcome measures along with additional questions regarding any treatment they may have received during the wait time (see Appendix R). Following the completion of the post-treatment outcome measures, participants who received the pamphlet condition will be called over the telephone. They will be asked if they are still interested in receiving TAICBT. If they are screened eligible to participate according to the original screening criteria, the full treatment will be offered.

4. What information about the research project and their role will participants be given during the initial contact?

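### The protocol sets three conflicting times for the post-treatment assessment; one of them, treatment completion, leaves TAICBT women who do not finish with no defined assessment

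*Protocol*

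**What the plan says.** The Analysis paragraph of the project summary rests efficacy on repeated-measures mixed-model ANOVAs of pre- and post-treatment scores. Four places bear on when the second score is taken.

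- **Project summary, Method.** One clock for both arms: "All other measures will be completed by both groups of participants at pre-treatment and post-treatment (10 weeks after baseline").
- **Section III, item 3, TAICBT treatment.** The trigger is an event: "In order to assess change over time, following treatment completion, participants will be emailed the same website link to fluidsurvey.com". No calendar limit is given. There are seven modules, "with each module taking approximately one week to complete". The same survey asks "questions regarding any additional treatment they sought over the 10-week period".
- **Section III, item 3, Pamphlet Condition.** The trigger is a range of dates: "Seven to ten weeks following baseline measures, the participants will be emailed the same website link to fluidsurvey.com".
- **Section II, item 1.** The wait is given as a single length: "Following the 10-week wait time, participants in the waitlist group will be re-screened". The Method paragraph and Section III give a wait of 7 to 10 weeks.

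A later telephone follow-up exists in the treatment arm only: "TAICBT participants will be contacted by telephone four weeks following treatment completion".

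**The concern.** The Section III paragraphs are the ones staff would use to send the surveys, and they put the two arms on different clocks. Two problems could follow.

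*Timing.* Depressive symptoms can change without therapy. If the arms are measured at different distances from baseline, part of the difference between them reflects elapsed time rather than treatment.

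*Selection.* Finishing the modules happens after randomisation, and only one arm can do it. If the survey goes out on completion, a woman who stops at module four has no date on which she is due one. The treatment arm could then consist of completers, set against a waitlist arm measured whatever happened. Choosing the analysis population later does not help, because surveys that were never sent cannot be recovered.

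A smaller effect is that Appendix R asks about other treatment over a 10-week period. A woman surveyed at week 7 has not yet lived through it.

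**Working it through.** The protocol states no figure that this point depends on, so there is none to reproduce. The main check is to compare the rules.

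| Place | Arm | Trigger | Implied week from baseline |
|---|---|---|---|
| Summary, Method | both | fixed date | 10 |
| Section III, item 3, TAICBT treatment | TAICBT | completion | about 7 (7 modules × about 1 week), no maximum |
| Section III, item 3, Pamphlet Condition | waitlist | date range | 7 to 10 |

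All three rules agree only if every TAICBT woman finishes at week 10 and every waitlist link goes out at week 10. A woman who finishes at week 7 is due at once under Section III and three weeks later under the Method paragraph. A woman still working at week 10 is due then under the Method paragraph and not yet under Section III. A woman who never finishes is due at week 10 under the first rule and never under the second.

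**Size of a timing difference (illustration).** Shift in the contrast = s × (TAICBT week − waitlist week), where s is natural improvement per week. The protocol does not give s. I assume 0.02 to 0.10 SD per week, linear and equal in both arms.

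- TAICBT at week 10, waitlist at week 7: 3 × 0.02 = 0.06 SD to 3 × 0.10 = 0.30 SD in favour of TAICBT.
- TAICBT at week 7, waitlist at week 10: the same 0.06 to 0.30 SD against TAICBT.
- TAICBT at week 10, waitlist spread evenly over weeks 7 to 10 (mean 8.5): 1.5 × 0.02 = 0.03 SD to 1.5 × 0.10 = 0.15 SD in favour of TAICBT.
- TAICBT after week 10: the gap can exceed 3 weeks, since completion has no limit.

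**Size of a selection effect (illustration).** If a fraction f of the TAICBT arm is unmeasured and would have scored k SD worse than those measured, the arm mean is too favourable by f × k. Neither value is in the protocol. With f from 0.20 to 0.40 and k = 0.5, the overstatement is 0.20 × 0.5 = 0.10 SD to 0.40 × 0.5 = 0.20 SD.

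**Loss of precision (illustration).** Take the planned 58 women as 29 per arm (the ratio is not stated) and a two-sided 5% test of two means. Power ≈ Φ(d√(n₁n₂/(n₁+n₂)) − 1.96). With all 29 measured in each arm, d = 0.8 gives Φ(0.8 × √14.5 − 1.96) = 0.86. If only 90% to 50% of the TAICBT arm is measured (26 down to 14 women), power falls to between 0.84 and 0.69. At d = 0.5 it falls from 0.48 to between 0.46 and 0.34.

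**The case against.** The strongest reply is that the design is not differential at all. The Method paragraph gives one time for both arms. Other text fits a 10-week clock: the TAICBT survey asks about a 10-week period, Section II gives a 10-week wait, and Appendix R has 10 weeks in its title. The expected treatment length also falls at the start of the waitlist window, so assessment dates may coincide in practice. Nothing says that non-finishers are not to be surveyed, and the consent forms, which are not shown, may cover them.

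Much of this stands. A reader might infer that the protocol has settled on measuring TAICBT women at completion, that follow-up time does differ by arm, and that the difference flatters the treatment. The documents do not support that. They show an unresolved contradiction, and on their own figures TAICBT could equally be measured earlier than the waitlist, which would work against it.

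The reply does not remove the contradiction. The common time is in the summary, while the instructions for sending the links say something else, and nothing says which governs.

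Two further limits are fair. The four-week follow-up concerns one arm and asks whether gains last after treatment ends, so it creates no between-arm timing bias. And because the Pamphlet Condition paragraph offers treatment only after the post-treatment survey, fixing the survey date bears on how long waitlist women wait. That is not a statistical decision.

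**Conclusion.** The point holds as a contradiction in data-collection rules that should be resolved before surveys are sent. Following Section III, assessment times may differ by arm and TAICBT non-finishers have no defined post-treatment assessment; following the Method paragraph, neither problem arises. The direction of any timing bias is open. Its size cannot be derived from the protocol, which gives no weekly improvement, SD or non-completion rate. The figures of 0.06 to 0.30 SD for a 3-week gap and 0.10 to 0.20 SD for selection rest wholly on the assumed inputs above and show only that the effect need not be negligible. It would fall on the main between-arm contrast.

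**What to change.** Reconcile the Method paragraph, Section II, item 1, and both parts of Section III, item 3 to:

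1. One outcome-assessment time for both arms, counted from baseline, with the same window in each. The Method paragraph already states a common 10-week point. Name the origin exactly, because under Section III the baseline measures are taken after allocation, so baseline and randomisation are different dates.
2. A survey sent to every randomised woman at that time, whatever number of modules she has finished.
3. A recall period in the other-treatment questions that matches the interval actually elapsed.

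The stated waits of 10 weeks and of 7 to 10 weeks must also be reconciled, but how long waitlist women wait before being offered treatment is for the investigators to decide. The telephone follow-up may stay anchored to the end of treatment.

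The cost is protocol wording and survey dates. Some women will be measured a few weeks after their last module, and others before they finish. With a week-10 assessment, a woman who finishes at week 7 would have her follow-up call at week 7 + 4 = 11, only one week after the survey; the report should acknowledge this.

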# Section IV: Access to Data and Findings

1. Who will have access to the original data? (For example: co-investigators, students). How will all those who have access to the data be made aware of their responsibilities concerning privacy and confidentiality?

The principal investigator, [name], and Unit Coordinator ([name]) will have access to the de-identified data for data entry and then for storage purposes. An undergraduate student who is seeking volunteer experience in our research lab may also be involved in data entry. He or she will be asked to sign a *Declaration of Confidentiality and Non-Disclosure* form that is required of all volunteers in the Online Therapy Unit (see Appendix S). When qualitative data are coded by the principal investigator and a second non-biased researcher, all identifying information will be removed from the participants’ responses to ensure privacy and confidentiality.

1. How do you anticipate disseminating your research results?
2. Directly to participants, describe how (e.g. website location of findings, location of published study, etc)

The results of this study will be published on the Online Therapy Unit’s website ([www.onlinetherapyuser.ca](http://www.onlinetherapyuser.ca)) and on our research lab’s website (<http://uregina.ca/~[name]/results.html>). This information is outlined in the consent form.

b) Check all others that apply:

Thesis/Dissertation/class presentation Media (e.g. newspaper, radio, TV) Presentations at scholarly meetings Published article, chapter or book

Internet Other, explain:

3. Describe your plans for protecting data as well as preserving or destroying data after the research is completed. For all data (e.g. paper records, audio or visual recordings, electronic recordings), indicate the:

a) means and location of storage (e.g. a locked filing cabinet, password protected computer files)

b) time duration of storage. (REB requires that data be archived for a minimum of three (3) years)

c) final disposition (archive, shredding, electronic file deletion)

(See Section IV-3 of the Guidelines)

In terms of clinical practice, the professional standard is to retain client records for a period of seven years. Hard-copy client records (i.e., the screening and assessment materials) will be locked in a secure cabinet and a secure office after data analysis and publication. E-mail correspondence between therapist and client will be retained on the secure website. The only individuals who can access this information will be the principal investigator ([name]), her supervisor ([name]), the client’s therapist if not [name], and the Online Therapy USER coordinator ([name]). After seven years, the paper records will be destroyed through shredding, and the e-mail correspondence will be downloaded and saved to a hard drive and then securely deleted.

APPENDIX B. PRE-SCREEN TELEPHONE INTERVIEW

[figure not shown]
**Pre-Screening Interview**

**Participant ID# Date:**

****Read Pre-Screening Script*(See Appendix X)***

***So now that you know about the formatting of the program and the research involved, does this still sound like something that you would be interested in?***

Yes (continue)

No… why? ___________________________________Screened out.

* IF SCREENED OUT REFER TO APPROPRIATE RESOURCES.

***Thanks for your interest in Maternal Depression Online. Can I ask how you heard about us?***

Referral from physician, social worker, nurse, other healthcare provider (not currently an eTherapist)

Referral from Intake (Health Region)

Referral from health care provider who is currently an eTherapist

**Name of e-therapist**______________________ **Agency:**______________________

Referral from another patient

Online advertisement: Which one? ___________________________

Newsletter: Which one? ___________________________________

Newspaper: Which one? __________________________________

Poster/brochure advertisement in community: Whereabouts? __________________________

Found Online Therapy USER website one own

Other; Please describe below:

**Limits of Confidentiality.**Before we begin our pre-screening interview, I have to inform you that although the interview will be confidential, there are certain limits to confidentiality including:

- If you pose an immediate threat to your life, or another individual’s life; or
- If you disclose information suggesting that any child is at risk of abuse, confidentiality will be broken.

   **Client understands confidentiality.**

| ***Demographic Data*** | | | | |
| --- | --- | --- | --- | --- |
| Client Name: | Date of Birth (DD/MM/YYYY) | | | |
| Address: | Appt #: | | | |
| City: | Postal Code: | | | |
| Phone No.:(home)  (work)  (other)  Phone No. during the day: | Can we contact you by: (Y or N)  Phone _______ Letter______  Leave Message____ **Email**____ | | | |
| Health Card No.: |  | | | |
| ***Exclusion Criteria*** | | | |  |
|  | | **Appropriate** | **Not Appropriate** |  |
| 1. Are you a Saskatchewan resident? | | Yes | No |  |
| 2. How old are you? _________ years | | Over 18 | Under 18 |  |
| 3. Do you have a **child** under the age of **one**? | | Yes | No |  |
| 4. Do you have access to a computer and printer at home? | | Yes | No |  |
| 5. Do you have access to the Internet at home? | | Yes | No |  |
| 6. Do you feel comfortable using the Internet? | | Yes | No |  |
| 7. Do you feel comfortable writing e-mails? | | Yes | No |  |
| 8. Would you be willing to have your physician, a medical clinic, or an emergency hospital be notified of your participation in this program?  Doctor’s Name:_________________________________  Medical Clinic:__________________________________  Telephone Number:_______________________________ | | Yes | No |  |

9. How far did you go in school?

Less than Grade 6  College/technical certificate; some university

Less than Grade 9  University undergraduate degree(s)

Less than Grade 12  University graduate degree(s)

High school diploma or GED

10. How comfortable would you say you are with writing out your thoughts and describing your feelings in words? Would you say you are…

| *Not very comfortable* | *A little comfortable* | *Somewhat comfortable* | *Fairly comfortable* | *Very comfortable* |
| --- | --- | --- | --- | --- |
| 1 | 2 | 3 | 4 | 5 |

11. Do you have any concerns about your ability to read or write?

______________________________________________________________________________

****Administer the EPDS. (Now I am going to ask you a few questions about your mood)****

APPENDIX C. EDINBURGH POSTNATAL DEPRESSION SCALE (EPDS)^[[1]](#footnote-1)^

| **As you have recently had a baby, we would like to know how you are feeling.  Please UNDERLINE the answer which comes closest to how you have felt  IN THE PAST 7 days, not just how you feel today.** |
| --- |

